#### Implementation outcomes

The RE-AIM (Reach, Effectiveness, Adoption, Implementation, and Maintenance) framework will be implemented as follows:
*Reach* will be measured by the number of people participating in the program divided by the number of people eligible to be recruited into the program.*Effectiveness* will be represented by the clinical outcomes.*Adoption* at the patient level will be measured by the proportion of people adherent to the clinical advice in lifestyle and self-care—this will be measured by the self-reported Summary of Diabetes Self-Care Activities (SDSCA) scale [32] at baseline, 6 months and 12 months (the SDSCA measure is a brief self-report questionnaire that includes items assessing general diet, specific diet, exercise, blood-glucose testing, foot care and smoking) and, in addition, the Diabetes Treatment Satisfaction Questionnaire (DTSQ) [33] will be administered at baseline, 6 months and 12 months (the DTSQ is the most commonly used patient-reported outcome in diabetes trials, which reflects the patient’s perception of the treatment)—and at the clinic level will be measured by the proportion of health clinics successfully recruited into the program over the clinics eligible and approached to participate in the program.*Implementation* will examine the fidelity and quality of the program execution per protocol. To check program fidelity, we will select and train standardized patients (SPs) from the program participants with stable conditions—these SPs will serve as the “secret agents” and the sentry to assess program fidelity with a quality checklist through their routine encounters with the clinicians at the DH diabetes clinic and the nurses; the clinicians will be blinded to the status of the SPs; and the development of SPs and the checklist will follow the protocol we have developed in a separate study [34].*Maintenance* will not be assessed for the purpose of this study.

The hospital and program administrative system will collect a range of other information including detailed program costs, health service utilization and incidence of complications and comorbidities. All data will be entered and securely stored in the EHR, a secured online data capturing and management system developed for the study at the DH.

### Sample size

In this proposed community-based intervention, changes in the HbA1c levels (continuous outcome) were considered for calculating the sample size for the individuals with diabetes and the incidence of diabetes (binary outcome) was considered for calculating the sample size for the individuals with prediabetes, respectively. For the individuals with diabetes, we aim to detect a clinically significant reduction in HbA1c levels from 7.6% to 6.5% (SD = 1.5%) (based on our assumption, the recommended effective diabetic management level and results of previous studies) among the individuals with diabetes during the 12-month period [35, 36] with medium effect size [37]. We expect a reduction of HbA1c to 7.0% in the control group, an optimal target level defined by the American Diabetes Association (ADA) [38]. Setting the statistical significance at the 0.05 level, seeking 90% power, with an intraclass correlation coefficient (ICC) of 0.01 based on a previous study conducted in Nepal [39], an average cluster size of 50 (individuals with diabetes) based on preliminary data from the awareness and screening campaign, a design effect for clustering of 1.49 and a design effect for unequal cluster size of 1.52 (coefficient of variation of cluster size 0.25), 91 people with diabetes per arm (182 total) will be required for the study. For the incidence of diabetes among people with prediabetes (dichotomous outcome), we considered the incidence of 10% and 2%, respectively, for the two groups; stated as a range in an earlier study [40]. Based on these considerations, 471 people with prediabetes per arm (942 total) will be required. We expect a dropout rate of 10% from baseline to 12-month follow-up; hence, we will need to recruit a total of 200 diabetes and 1036 prediabetes participants (total sample size = 1236 participants). The sample size for our cluster RCT was calculated using the following equation. Details of the sample size estimation is available in another study conducted by Ribeiro et al. [41]:
$$ {\mathrm{SS}}_{\mathrm{cluster}\ \mathrm{RCT}}={\mathrm{SS}}_{\mathrm{standard}\ \mathrm{RCT}}\times {\mathrm{DE}}_{\mathrm{cluster}}\times {\mathrm{DE}}_{\mathrm{unequal}} $$where SS_cluster RCT_ = total sample size for a cluster RCT; SS_standard RCT_ = total sample size for a standard RCT (equal to (Z_1 – α / 2_ + Z_1 − β_)^2^ 2σ^2^ / Δ^2^, where *Z*_*x*_ is the *x*th percentage point of the standard normal distribution, Δ is the clinically important difference in treatment means and σ^2^ is the variance in the outcome); DE_cluster_ = design effect for clustering (equal to 1 + ICC × (m – 1), where *m* is the number per site); and DE_unequal_ = design effect for unequal cluster size (equal to 1 + [(1 + *cv*^2^) × *m* − 1] × ICC, where *cv* is the coefficient of variation of cluster size and *m* is the mean cluster size).

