### Outcome measures

We will examine both clinical outcomes and implementation outcomes as we hypothesize that the nurse-led continuum of care program will improve both health and the implementation of priority interventions in diabetes. The outcome measure will pertain to the individual participant level. The primary outcome for the diabetes group is the HbA1c level at 12 months from the intervention. The HbA1c level is indicative of the average level of blood glucose over the past 2–3 months [22]. The primary outcome for the prediabetes group is the incidence of diabetes at 12 months from the intervention.

The secondary outcomes are blood pressure, body mass index (BMI) and lipid levels. Also, the secondary outcomes include a series of implementation outcomes in the RE-AIM (reach, effectiveness, adoption, implementation, and maintenance) implementation framework [23–25]. We provide details on those measures in the following (see Table 2 for a summary).

**Table 2 Tab2:** Measures of outcome variables

	Assessment method	Assessor	Baseline	Midline (6 months)	End line (12 months)	Variable

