### Statistical analysis

Data will be analyzed at the individual (patient) level. Statistical analyses will be performed using the intention-to-treat (ITT) approach in the originally assigned groups. Demographic and baseline characteristics for the intervention and control groups will be presented in the form of mean (standard deviation (SD)) or 95% confidence intervals (CIs) for continuous variables and counts (percentages) for categorical variables. ITT analysis will be performed on the final data collected at 12 months.

Generalized estimating equations (GEEs) with clustering by site, an exchangeable correlation matrix and robust variances will be used to assess the program effect adjusting for potential baseline covariates. The model will take account of clustering and will be used to look at the difference between groups for the HbA1c level at 6 and 12 months, respectively. Multiple imputation will be used to account for the missing values assuming they are missing at random. To test for the secondary sensitivity analysis, data will be analyzed without multiple imputation and without baseline covariate adjustment. The difference in the incidence of diabetes between the groups among the individuals with prediabetes will be tested using a GEE. Statistical significance will be assessed at the 5% level and all analyses will be two-sided. All data analyses will be performed using the Stata 15 (StataCorp, TX, USA) statistical software program.

As we expect that the program effect may differ between several subgroups of the program participants, we plan to do secondary analyses of the following three subgroups for the primary (HbA1C) and secondary (incidence of diabetes) outcomes: the subgroups with poor initial glycemic level (HbA1c ≥ 5.7%) (people with poorer glycemic level at baseline may have a stronger desire to change their behavior); the subgroups divided by gender (in Nepal, women tend to be more adherent to clinician guidance); the subgroups of different social economic classes (people in higher socioeconomic class may be more likely to adhere to lifestyle changes); and government versus nongovernment health centers. The secondary analyses will compare the HbA1c level and incidence of diabetes among people with prediabetes among these subgroups at the end of the 12-month intervention using the generalized linear mixed models with a random cluster effect and adjusting for potential confounders.

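### The diabetes sample size of 91 per arm uses a 1.1-point before-after fall as the between-arm difference; for the plan's own 0.5-point difference, unadjusted power is about 58%, not 90%

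*Protocol article*

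**What the plan says.** All statements are from the protocol article.

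- **Target (Sample size):** "we aim to detect a clinically significant reduction in HbA1c levels from 7.6% to 6.5% (SD = 1.5".
- **Control arm (Sample size):** "We expect a reduction of HbA1c to 7.0% in the control group".
- **Error rates (Sample size; Statistical analysis):** "Setting the statistical significance at the 0.05 level, seeking 90% power". Testing is two-sided: "Statistical significance will be assessed at the 5% level and all analyses will be two-sided".
- **Formula (Sample size):** the individually randomised size is (Z for 1 − α/2 plus Z for 1 − β)² × 2σ²/Δ², where "Δ is the clinically important difference in treatment means". It is then multiplied by a design effect for clustering (1.49) and one for unequal cluster size (1.52), from ICC 0.01, mean cluster size 50 and coefficient of variation 0.25.
- **Result (Sample size):** "91 people with diabetes per arm (182 total) will be required for the study". With 10% dropout, 200 people with diabetes are to be recruited; the abstract gives the same 200.
- **Outcome (Outcome measures):** "The primary outcome for the diabetes group is the HbA1c level at 12 months from the intervention". The Statistical analysis section compares HbA1c between groups with a GEE adjusted for baseline covariates.
- **Clusters (Setting):** 13 per arm, 26 in all.

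**The concern.** The formula needs the expected gap between the arms at 12 months. The section supplies both 12-month means, 6.5% as the target and 7.0% for control, so that gap is 0.5 points. The fall from 7.6% to 6.5% is a change over time and includes improvement that the plan expects without the nurse-led programme. Control sites also receive the awareness campaigns, screening and improved hospital care (Table 1), so a fall there fits the design.

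Required size varies with 1/Δ², so using 1.1 in place of 0.5 divides the uninflated size by (1.1/0.5)² = 4.84. At stake is whether the diabetes primary outcome has the power claimed for it, and how a result that misses significance should be read.

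**Working it through.** **Inputs.** Two-sided α 0.05 and power 90%, so (1.96 + 1.2816)² = 10.507. SD 1.5, ICC 0.01, coefficient of variation 0.25, 26 clusters, 91 per arm. All are from the sections cited above.

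**1. Reproduce the stated figure with Δ = 1.1.**
- 10.507 × 2 × 1.5² / 1.1² = 39.1, rounded up to 40.
- 40 × 1.49 × 1.52 = 90.6, so 91 per arm. This is the stated number.

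**2. Same formula with Δ = 0.5.**
- 10.507 × 2 × 1.5² / 0.5² = 189.1, rounded up to 190 per arm before any clustering allowance. That alone is more than twice 91.
- Keeping Δ = 0.5 and trying 80% power, a one-sided test or a single design effect, alone or combined, gives 167 to 352 per arm. None gives 91, so the input was 1.1.

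**3. Does reading the outcome as change help?** The abstract speaks of change in HbA1c. From a common baseline of 7.6% the falls are 7.6 − 6.5 = 1.1 and 7.6 − 7.0 = 0.6. Their difference is again 0.5.

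**4. Design effect at the size the trial would have.**
- Mean cluster size: 182 / 26 = 7.
- The plan's unequal-size formula: 1 + [(1 + 0.25²) × 7 − 1] × 0.01 = 1.064.

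**5. Unadjusted power for 0.5 points, 91 analysed per arm.**
- SE = 1.5 × √(2 × 1.064 / 91) = 0.229.
- 0.5 / 0.229 = 2.18, and 2.18 − 1.96 = 0.22, so power is about 58.7%.
- With 90 per arm (200 recruited less 10%) it is 58.2%. With a t reference on 24 degrees of freedom and 91 per arm it is 55.2%. With no clustering at all it is 61.4%.

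**6. Difference detectable with 90% power.** (1.96 + 1.2816) × 0.229 = 0.74 with 91 per arm and 0.75 with 90 per arm.

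**7. Gain from adjusting for baseline HbA1c.** If 1.5 is the SD of the 12-month value, the residual SD is 1.5 × √(1 − ρ²). The documents give no correlation ρ, so these values are assumptions:

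| ρ (assumed) | Power for 0.5 points, 91 per arm, design effect 1.064 |
|---|---|
| 0.3 | 63% |
| 0.5 | 71% |
| 0.7 | 86% |

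**8. Size needed for 90% unadjusted power at 0.5 points with 13 clusters per arm.** At 222 analysed per arm the mean cluster size is 17.1 and the design effect 1.17. Then 189.1 × 1.17 is about 222, so the figure is self-consistent.

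**The case against.** Three arguments on the other side have weight.

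**Baseline adjustment.** The main GEE adjusts for baseline covariates, and the unadjusted analysis is a sensitivity analysis, so 58% is not a ceiling. This stands. However, the article does not name baseline HbA1c among the covariates, gives no correlation and claims no such gain. If 1.5 is already the SD of change, step 7 does not apply as calculated. Over the assumed correlations power stays below 90%.

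**Generous design effects.** The plan assumes 50 people per cluster and multiplies two factors that each contain the ICC inflation, so clustering is counted twice. This overstates the size and partly offsets the wrong contrast. It does not cure it: the 58% already credits the trial with its small clusters, and ignoring clustering altogether gives only 61%.

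**Enrolment may not stop at 200.** The Screening and recruitment section invites everyone with HbA1c of at least 5.7% and expects 1050 people with diabetes. If all 1050 enrolled and 10% dropped out (about 472 per arm, about 36 per cluster, design effect about 1.38), unadjusted power for 0.5 points would be about 99%. This also stands. But the abstract and the Sample size section both give 200 as the number to recruit, so 200 is the natural reading.

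A reader might also go further and apply the plan's own multipliers to Δ = 0.5. That gives power of about 45% (design effect 1.52) or 32% (product 2.26), and 190 × 1.49 × 1.52 = 430.3, so 431 per arm. The documents do not support these as estimates for this trial: they presuppose 50 per cluster where 182 over 26 is 7, and the product double-counts clustering. Nor can one say that a true 0.5-point effect would more likely than not be missed; at 58% it is somewhat more likely to be detected.

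**Conclusion.** The calculation is wrong as written. The stated size rests on a within-arm change, while the formula, the primary outcome and the analysis all concern a between-arm difference, which the plan's own targets put at 0.5 points. Since the inputs, formula and result are all printed, this is a contradiction within the article and not a detail left to a fuller document.

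The size of the problem is unadjusted power of about 58% against 90% claimed, and a detectable difference half as large again as the one planned. This rests on SD 1.5, ICC 0.01, coefficient of variation 0.25, 26 clusters and about 180 people analysed. It does not show that the trial cannot reach 90%: both a strong baseline correlation and enrolment well above 200 would narrow or remove the gap, but the plan commits to neither.

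**What to change.** In the Sample size section:

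1. Replace the 1.1-point contrast with the between-arm difference of 0.5.
2. Restate power and detectable difference for about 180 analysed, using the cluster size that the trial will actually have: unadjusted, about 58% for 0.5 points, or 90% for about 0.75 points.
3. Say whether 1.5 is the SD of the 12-month value or of the change, and give any assumed baseline to 12-month correlation with the power that follows.
4. State whether 200 is a cap, and reconcile it with the 1050 expected from screening.

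In the Statistical analysis section, name baseline HbA1c as a covariate in the primary model.

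The cost is a rewritten paragraph and a less favourable stated power. The restatement needs no extra patients. If the sponsor wants 90% unadjusted power for 0.5 points, about 222 analysed per arm would be needed, within the pool that the plan expects. The Trial status section says that recruitment had not begun, so this could be settled before enrolment.

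### The sample size formula counts clustering twice (2.27 instead of 1.52 at 50 per cluster), and 50 people with diabetes per cluster does not fit 200 in 26 clusters; the error is conservative, so power should be restated and recruitment kept

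*Protocol article*

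**What the plan says.** All of this is in the Sample size section of the protocol article unless stated otherwise.

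- The trial size is the size for an individually randomized trial times a clustering factor, 1 + ICC × (m − 1), times a second factor, the "design effect for unequal cluster size (equal to 1" + [(1 + cv²) × m − 1] × ICC).
- The inputs are ICC 0.01 and "an average cluster size of 50 (individuals with diabetes) based on preliminary data from the awareness and screening campaign". They yield "a design effect for clustering of 1.49 and a design effect for unequal cluster size of 1.52 (coefficient of variation of cluster size 0.25").
- The error rates are given as "Setting the statistical significance at the 0.05 level" and "seeking 90% power". The Statistical analysis section adds: "Statistical significance will be assessed at the 5% level and all analyses will be two-sided".
- For prediabetes, "we considered the incidence of 10% and 2%, respectively, for the two groups; stated as a range in an earlier study".
- The results are 91 per arm (182 in total) for diabetes and 471 per arm (942) for prediabetes. After 10% dropout, "we will need to recruit a total of 200 diabetes and 1036 prediabetes participants (total sample size = 1236 participants").
- The Setting section fixes 26 clusters, 13 per arm.

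**The concern.** The second factor is the usual complete design effect for clusters of unequal size. Put cv = 0 into it and it becomes 1 + (m − 1) × ICC, which is the first factor. It should replace the first factor and not multiply it. As printed, a trial with perfectly equal clusters would be inflated by the square of its design effect.

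The cluster size is a second problem. Fifty people with diabetes in each of 26 clusters would be 1,300 people, while the plan recruits 200.

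At stake is whether the 90% power claimed for the two primary clinical outcomes describes this trial. A reader needs true power to judge a null result, and needs to know whether the prediabetes cohort depends on the large contrast of 10% versus 2%.

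**Working it through.** **Inputs.** Two-sided alpha 0.05; power 90%; ICC 0.01; cv 0.25; m = 50; HbA1c change 7.6% to 6.5% = 1.1 with SD 1.5; incidence 10% and 2%; 26 clusters; dropout 10%. All are from the sections named above.

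**1. The plan's own figures**
- Clustering factor: 1 + 0.01 × 49 = 1.49.
- Unequal-size factor: 1 + (1.0625 × 50 − 1) × 0.01 = 1.521.
- Product: 1.49 × 1.521 = 2.27.
- Diabetes: (1.960 + 1.282)² × 2 × 1.5² / 1.1² = 39.1, rounded up to 40 per arm. 40 × 2.267 = 90.7, stated 91.
- Prediabetes: the two-proportion formula gives 184 per arm, or 208 with continuity correction. 208 × 1.49 × 1.52 = 471.1, stated 471. Without the correction, 184 × 2.267 = 417, which does not match.
- One factor alone gives about 60 to 61 and 310 to 316 per arm, so it reproduces neither stated figure.

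The product was therefore used for both cohorts. The reuse of m = 50 for prediabetes is inferred from this match; the text does not state it.

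**2. Cluster sizes implied by the plan**

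| Cohort | Recruited / 26 | Single design effect | Analysed / 26 | Single design effect |
|---|---|---|---|---|
| Diabetes | 200/26 = 7.7 | 1.07 | 180/26 = 6.9 | 1.06 |
| Prediabetes | 1036/26 = 39.8 | 1.41 | 932/26 = 35.8 | 1.37 |

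The factor applied was 2.27. Even the 1,050 people with diabetes that the Screening and recruitment section expects to identify would be about 40 per cluster.

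**3. Prediabetes power, 466 analysed per arm.** The effective size is nₑ = 466 / design effect; at ICC 0.01 it is 466 / 1.371 = 340. With Δ the difference in incidence and p̄ the mean of p₁ and p₂, power = Φ{[Δ√nₑ − 1.96 √(2p̄(1 − p̄))] / √(p₁(1 − p₁) + p₂(1 − p₂))}. The continuity-corrected version replaces Δ by Δ − 1/nₑ. ICCs above 0.01 are my assumptions, to show the range.

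| ICC | Design effect | nₑ | 10% vs 2%, uncorrected / corrected | 10% vs 5%, uncorrected / corrected |
|---|---|---|---|---|
| 0.01 | 1.371 | 340 | 99.3% / 98.9% | 70% / 64% |
| 0.02 | 1.742 | 268 | 97% / 96% | 59% / 53% |
| 0.03 | 2.113 | 221 | 94% / 92% | 51% / 44% |
| 0.05 | 2.854 | 163 | 86% / 81% | 40% / 32% |

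At ICC 0.01, 90% power is reached for 10% versus about 3.7% uncorrected, or about 3.5% corrected. The two methods must not be mixed: on the corrected method, 10% versus 3.7% has 87.5% power.

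**4. Diabetes power, 90 analysed per arm.** nₑ = 90 / 1.064 = 84.6. Power = Φ[Δ / (1.5 √(2/nₑ)) − 1.96].
- Δ = 1.1, the change used for sizing: above 99%.
- Δ = 7.0 − 6.5 = 0.5, the difference between the stated arm expectations: about 58%.
- Sized for 1.1 with one design effect at m = 7, the requirement would be 40 × 1.064, about 43 per arm. For 0.5, solved with 13 clusters per arm, it is about 222 per arm.

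**5. Dropout.** 182 × 1.1 = 200.2 and 942 × 1.1 = 1036.2 give the stated targets. Losing 10% leaves 180 and 932 (1036 × 0.9 = 932.4), slightly below 182 and 942.

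**The case against.** Four points can be made for the plan.

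- **The error is conservative.** This stands. On the protocol's own effect sizes both cohorts exceed 90% power. A reader might infer that a wrong design effect leaves the trial underpowered; the documents do not support that for this error alone.
- **Fifty per cluster is about right overall.** The two cohorts together give 1236/26 = 47.5. But the protocol labels the 50 as individuals with diabetes, and each primary outcome belongs to one cohort. What stands is that the prediabetes mismatch is modest (39.8 against 50, or 1.41 against 1.52), so double counting is the main error there. It would be too strong to say that the planned numbers cannot come near 50 in any sense.
- **The surplus protects against a higher ICC.** This stands in part. At 35.8 per cluster, a single design effect of 2.27 corresponds to an ICC of about 0.034. The excess works as a margin, but an undeclared one. A restatement that spends all of it on a smaller effect at ICC 0.01 would be optimistic, so higher ICCs should be shown.
- **The dropout shortfall is trivial.** It is 2 of 182 and 10 of 942. That stands, and it is only a matter of wording. Dividing by 0.9 would give 203 and 1047, but these inflate totals that are themselves wrong, so they are not better targets.

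**Conclusion.** The formula is wrong as printed, and the error entered both stated sample sizes: 2.27 was applied where 1.52 holds at m = 50, and about 1.07 (diabetes) and 1.37 to 1.41 (prediabetes) at the planned cluster sizes. The 50 people with diabetes per cluster contradicts 200 in 26 clusters. The stated 90% is not the power of either cohort. For prediabetes at 10% versus 2% it is about 99%, so the cohort need not rest on an 80% relative reduction, although it gives only 64 to 70% at 10% versus 5%.

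A tempting further reading is that the trial may recruit fewer people. The documents do not support it. The diabetes size rests on a 1.1-point change, while the stated arm expectations differ by 0.5, and at 0.5 the planned number gives about 58%. That is a separate problem, which the excess inflation partly hides.

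These figures assume ICC 0.01, cv 0.25, equal arms, 10% loss and large-sample normal formulas with no allowance for having only 26 clusters. The arithmetic of the double counting depends on none of the power assumptions.

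**What to change.** 1. Delete the clustering factor from the equation. Use the unequal-size factor alone, with m for each cohort taken as its own participants divided by 26.
2. Keep 200 and 1036 as minimum recruitment targets; do not reduce either because of this correction.
3. Restate prediabetes power by one named method. At ICC 0.01 and 466 analysed per arm, this is 90% for 10% versus about 3.5% (continuity-corrected) or 3.7% (uncorrected), and 64% or 70% for 10% versus 5%. Show the same at higher ICCs.
4. Restate diabetes power in the same revision as the between-arm difference: about 58% for 0.5 points with 90 analysed per arm. Decide on the diabetes sample size from that figure.
5. Give the numbers expected for analysis after 10% dropout as 180 and 932.

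The cost is one rewritten paragraph and one equation, with no change to conduct. The Trial status section says recruitment has not begun, so this can be done before enrolment. Any increase in the diabetes cohort would be a separate decision, prompted by the 0.5-point difference and not by this correction.

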**Methods:**

We will conduct a two-arm, parallel group, stratified cluster randomized controlled trial of the NUrse-led COntinuum of care for people with Diabetes (*N*_1_ = 200) and prediabetes (*N*_2_ = 1036) (NUCOD) program, with primary care centers (9 outreach centers and 17 government health posts) as a unit of randomization. The NUCOD program will be delivered through the trained diabetes nurses in the community to the intervention group and the outcomes will be compared with the usual treatment group at 6 and 12 months of the intervention. The primary outcome will be the change in glycated hemoglobin (HbA1c) level among diabetes individuals and progression to type 2 diabetes among prediabetes individuals, and implementation outcomes measured using the RE-AIM (reach, effectiveness, adoption, implementation and maintenance) framework. Outcomes will be analyzed on an intention-to-treat basis.

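### The 10% dropout allowance multiplies by 1.1 where it should divide by 0.9, so 200 and 1036 recruits fall slightly short of the 182 and 942 the plan requires

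*Protocol article*

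**What the plan says.** The Sample size section of the protocol article gives a requirement for each cohort before any loss. For diabetes: "91 people with diabetes per arm (182 total) will be required for the study". For prediabetes: "471 people with prediabetes per arm (942 total) will be required". The dropout assumption comes next: "We expect a dropout rate of 10% from baseline to 12-month follow-up". From it the section concludes: "we will need to recruit a total of 200 diabetes and 1036 prediabetes participants (total sample size = 1236 participants". The Methods paragraph of the abstract carries the same 200 and 1036 as the sizes of the two cohorts.

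The section states no formula for the dropout step. The displayed equation covers only the individually randomised sample size and the two design effects.

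**The concern.** A dropout rate counted from baseline applies to the people recruited. To finish with N completers after losing a fraction d, a trial must recruit N/(1 − d). Multiplying N by (1 + d) always gives too few, because the loss is then taken from the larger number.

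If that happened here, the recruitment targets in the abstract and the Sample size section do not follow from the stated requirement and the stated dropout. The step is also separate from how 182 and 942 were obtained, so revising those base sizes would not correct it.

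**Working it through.** **Inputs.** All come from the protocol article. Sample size section: 182 and 942 required, 10% dropout, 200 and 1036 to recruit, SD 1.5, HbA1c 7.6% to 6.5% (a change of 1.1), incidence 10% versus 2%, design effects 1.49 and 1.52, and "Setting the statistical significance at the 0.05 level, seeking 90% power". Statistical analysis section: two-sided tests.

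**1. Base sizes contain no dropout term.**
- Diabetes: 2 × 1.5² × (1.960 + 1.282)² / 1.1² = 39.08, rounded up to 40 per arm. Then 40 × 1.49 × 1.52 = 90.6, so 91 per arm and 182 in total.
- Prediabetes: the usual two-proportion formula gives 183.1 per arm, or 207.4 with a continuity correction, rounded up to 208. Then 208 × 1.49 × 1.52 = 471.1, so 471 per arm and 942 in total. The article does not mention the continuity correction. It is inferred because the figure reproduces with it and not without it (184 × 1.49 × 1.52 = 416.7).

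Both stated figures reproduce without any allowance for loss, so dropout enters only afterwards.

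**2. The dropout step.**

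| | Diabetes | Prediabetes |
|---|---|---|
| Required, N | 182 | 942 |
| N × 1.1 | 200.2 | 1036.2 |
| Stated target | 200 | 1036 |
| N / 0.9 | 202.2 | 1046.7 |

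Multiplication by 1.1 matches both stated totals to the unit. Division by 0.9 matches neither.

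**3. Completers at 10% dropout.**
- Diabetes: 200 × 0.9 = 180, which is 2 below 182.
- Prediabetes: 1036 × 0.9 = 932.4, about 10 below 942.

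The highest dropout at which the targets still meet the requirement is 1 − 182/200 = 9.0% and 1 − 942/1036 = 9.1%.

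**4. Effect on power.**
- If 182 and 942 each gave exactly 90%, power at the reduced number would be Φ(3.2415 × √(ratio) − 1.960). The ratios are 180/182 = 0.989 and 932.4/942 = 0.990. Both give about 89.7%, a loss of 0.3 points.
- Diabetes, on the plan's formula with a difference of 1.1: the effective size per arm is 182/2/(1.49 × 1.52) = 40.18, giving 90.8%. With 180 it is 39.74, giving 90.5%.
- Prediabetes, without continuity correction: 93.3% at 942 and 93.0% at 932.4.

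**5. Need before intermediate rounding.**
- Diabetes: 2 × 39.08 × 1.49 × 1.52 = 177.0 in total, so 180 exceeds it.
- Prediabetes: 2 × 207.35 × 1.49 × 1.52 = 939 with the continuity correction, so 932 is about 7 short. Without it, 2 × 183.1 × 1.49 × 1.52 = 829, which 932 exceeds.

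**6. Corrected totals on the present base.** 182/0.9 rounds up to 203 and 942/0.9 to 1047, together 1250. With equal arms they are 204 (102 each) and 1048 (524 each), together 1252. The stated total is 1236, so the difference is 14 to 16 participants.

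**The case against.** A reader might infer that the trial cannot reach its stated 90% power with these targets. The document does not support that. For diabetes, 182 is itself inflated by rounding 39.08 up to 40 before the design effects are applied. The unrounded need is 177.0, and 180 completers clear it. For prediabetes, a shortfall against 90% appears only under a continuity correction that the article does not mention, and it is then about 7 people, under 1%. This part of the objection stands and limits the point to a small arithmetic slip.

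Other defences have less force:

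- **The factor of 1.1 is inferred.** True, since no formula is stated. The shortfall does not depend on it: 180 < 182 and 932.4 < 942 whatever route was taken.
- **Completers are not the whole analysis set.** The Statistical analysis section plans intention-to-treat with multiple imputation, and HbA1c is also measured at 6 months, so a participant missing at 12 months may still contribute. Imputation does not, however, turn 180 observed outcomes into 182. The same section also plans an analysis without imputation, and by inflating for dropout the plan itself treats 182 and 942 as numbers needed after loss.
- **Recruitment may exceed the targets.** The Screening and recruitment section expects to identify 1050 people with diabetes and 1625 with prediabetes, and invites everyone with HbA1c of 5.7% or more. The extra participants therefore look available, and nothing suggests that recruitment is infeasible. That does not make 200 and 1036 follow from 182, 942 and 10%.
- **10% is a round guess, and 9% lies within its precision.** Fair as to importance, but the stated conclusion still contradicts its stated inputs.

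**Conclusion.** The point holds as a minor arithmetic error. At the plan's own 10% dropout, the recruitment totals leave 2 fewer people with diabetes and about 10 fewer with prediabetes than the plan says it requires, about 1% in each cohort. The targets tolerate dropout of about 9.0% and 9.1%, not 10%. The cost is about 0.3 percentage points of power per cohort. It does not bring the diabetes cohort below 90% on the plan's own formula and inputs, and it does not threaten the trial's conclusions.

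The counts assume only that the 10% applies to those recruited, as the wording from baseline to 12 months implies, and that 182 and 942 are taken as stated. The power figures further assume the inputs that reproduce 91 and 471 per arm. For diabetes that means a difference of 1.1, although the same section expects the arms to reach 7.0% and 6.5%, a difference of 0.5. Whether the base sizes are sound is a separate and larger question. The dropout step needs correcting whatever the answer.

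**What to change.** In the Sample size section, state that 200 and 1036 recruits provide 182 and 942 completers only if dropout is about 9% or less, and that about 180 and 932 are expected at 10%. This costs one sentence and makes the stated dropout tolerance slightly less favourable.

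If the base sizes are recalculated, divide by (1 − dropout) rather than multiplying by (1 + dropout). On the present base sizes that gives 203 and 1047, or 204 and 1048 with equal arms. If the targets themselves are raised, the abstract and the overall total of 1236 must change with them, at a cost of 14 to 16 more participants. The Trial status section says recruitment has not started, so either course is open.
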